#### 4.4 Follow-up and withdrawals

Availability of follow-up data will be presented descriptively as frequency and percentages at each time-point and for each assessment in each randomised group.

Withdrawals from follow-up will be tabulated, noting whether the participant allowed continued use of routinely collected data or not and the time-point of withdrawal. Time to withdrawal will also be summarised using Kaplan-Meier curves.

##### Example Table: Withdrawals from follow-up

*Data are n; %, unless otherwise stated*

|                                                                               | Conservative strategy
(N=) | Invasive strategy
(N=) | Overall
(N=) |
|-------------------------------------------------------------------------------|-------------------------------|---------------------------|-----------------|
| Withdrawn from follow up but allow the use of routinely collected data        |                               |                           |                 |
| < 12 months follow up                                                         |                               |                           |                 |
| ≥ 12 months follow up                                                         |                               |                           |                 |
| Withdrawn from follow up and not allowing the use of routinely collected data |                               |                           |                 |
| < 12 months follow up                                                         |                               |                           |                 |
| ≥ 12 months follow up                                                         |                               |                           |                 |

Duration of follow-up will be calculated using the reverse Kaplan-Meier method (the failure event will be 1 for those remaining in the study and 0 for those who have died or withdrawn from any further use of data), patients who have died will be censored at date of death and patients withdrawn from follow up and not allowing the use of routinely collected data censored at their last assessment date. Data will be presented as median (with 95% confidence interval) and interquartile range (IQR), both overall and within each randomised treatment group.

#### 4.5 Protocol deviations

Protocol deviations will be reported overall and by randomised group. Details of protocol deviations will be reported in a line listing, sorted by type or summarised by frequency and percentage of patients reporting a particular type of deviation by randomised group if the number of that type of deviations is high and the impact low (e.g. for study visits taking place outside of allowable time-windows). Note that protocol deviations which are administrative in nature (e.g. patient identifiable data sent to an unsecure email address, incorrect versions of consent forms being signed etc.) will not be included as part of the statistical reporting.

## 5. ANALYSIS METHODS

### 5.1 Analysis of primary outcome

#### 5.1.1 Main analysis methods

Event rates will be estimated using Kaplan-Meier methods and will be presented using Kaplan-Meier survival curves. Analyses will utilise all data collected, up to a maximum of 5 years post randomisation. Kaplan-Meier estimates of 6-month and 1-year event rates will be reported in each treatment group alongside 95% CI's.

The primary analysis will be conducted in the ITT population. The difference in survival between treatment groups will be compared using a non-parametric stratified log-rank test (stratified by Rockwood frailty status at randomisation\*). An adjusted Cox proportional hazards regression model (adjusted by Rockwood frailty status at randomisation\*) will be used to estimate treatment effect. A hazard ratio (HR) <1 will indicate a reduction in the event rate in the invasive treatment group and will be presented alongside a 95% CI.

A further multivariable model will also be used, as a sensitivity analysis, to also adjust for sex, age at trial entry, MoCA status at baseline and recruiting centre (which will be added to the model as a shared frailty term).

*\*in the event of an error at randomisation, the correct frailty strata will be used, rather than that entered into the randomisation system.*

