### 6.3. Randomisation

Following consent, patients will be randomised to an invasive strategy (coronary angiography and, if appropriate, coronary revascularisation [PCI or CABG] plus optimal medical therapy) or to conservative management (optimal medical therapy alone). Randomization will be on 1:1 per patient basis using a variable-length block stratified method specified by the statistics team. Stratification will be by site and Frailty score: frail (Rockwood Frailty Score  $\geq 5$ ) and not frail (Rockwood Frailty Score  $< 5$ ) (**Appendix 16.4**)

Randomisation will be performed at site using a secure web-based system. This system will produce a randomisation number which will need to be recorded on MACRO. Sites must complete the Patient Enrolment log and Patient Identification Code List.

For each randomised participant, the following information will be collected:

- Participant or Consultee Consent form
- Eligibility criteria form

The above documents should be transmitted by secure fax to the NCTU on [name] (SoHo 66), or by email to [[contact]](mailto:[contact]) using an NHS.net email. If the site does not use nhs.net email, the documents should be sent as an encrypted, password-protected file (with the password sent in a separate email) to [[contact]](mailto:[contact]).

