## 2.3 Randomisation and blinding

Patients are randomised to invasive or conservative management on a 1:1 basis using a variable-length block stratified method. Block lengths used are documented in the statistical section of the TMF. Randomisation is performed at site using a secure web-based system.

Up to 14th September 2018 stratification was based on three factors:

- Recruiting centre
- Frailty score: frail (Rockwood Frailty Score  $\geq 5$ ) and not frail (Rockwood Frailty Score  $< 5$ )
- Cognitive impairment: impaired (Montreal Cognitive Assessment (MoCA) score  $< 26$ ) and not impaired (MoCA  $\geq 26$ ).

At the time data were first presented to the data monitoring committee (DMC) on 30th June 2017, a small proportion (~7%) of patients were found to have been randomised to the incorrect cognitive impairment strata. At the time of the next DMC meeting, this had increased to ~13%. On investigation, it became apparent that some sites found it logistically challenging to obtain a complete 30-item MoCA assessment from the participant prior to randomisation. So as not to delay treatment, randomisation was going ahead without a complete MoCA assessment being carried out, with cognitive impairment judged by the treating clinician for the purpose of randomisation and the MoCA assessment completed after randomisation. This was leading to a number of protocol deviations.

The decision was therefore made to remove cognitive impairment as a stratification factor. This was incorporated into protocol version 2.0 [14/12/17]. However due to a delay in updating the randomisation system, this was not implemented in practice until 14th September 2018, following the implementation of all other aspects of protocol version 2.0 on 20th February 2018. In total, 532 participants were recruited under the original allocation strategy.

The update to the randomisation system involved creating new blocks of participants, with variable block lengths as before. Incomplete blocks using the old strata were not used. The overall sample size should ensure this change has minimal or negligible effect on the overall balance between randomised groups at the end of the study.

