### Updated sample size calculation

In late 2018, an assessment of study progress was made by the trial management group and the trial steering committee. It was accepted that recruitment was at a much slower rate than originally projected and the study would require a considerable extension to recruitment in order to reach the target sample size of 2300. Furthermore, a blind review of available primary outcome data (unadjudicated) to December 2018 suggested the probability of an event in the first year (aggregated across treatment groups) was lower than originally anticipated at approximately 20%.

The original sample size calculation effectively assumes patients are only followed-up for 12 months. However, in reality, patients are followed up throughout the trial, not just to 12 months, and the analysis will make use of all data available on all patients. This allows events to accrue over a longer period, so fewer patients would need to be recruited to achieve the required number of events.

A more realistic approach to sample size estimation, as detailed in Barthel *et al.*, 2006, allows events beyond one-year to be incorporated by assuming the event rate follows a piecewise exponential distribution; the recruitment rate across the trial can also be taken into account as this will inform the duration of follow up available for each patient at the time of the primary analysis. This approach can be implemented using the Stata function ARTSURV (version 1.1.0).

Assuming an event rate of 20% in the conservative therapy arm at 12 months and maintaining the original clinically relevant effect size of a 20% reduction equates to an event rate of 16% in the invasive therapy arm and a HR of 0.78. To detect a HR of 0.78 with 90% power and 5% two-sided type I error requires around 700 events to be observed.

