If the original recruitment period is extended for 24 months (i.e. a total recruitment period of 5 years) and a recruitment rate of 32 patients/month can be maintained then the study will recruit 1668 patients and have 92.5% power (5% two-sided type I error) to observe a HR of 0.78 assuming an event rate in the control group of 20% with the analysis taking place 1 year after the last patient is recruited and utilising all available follow-up data. This assumes a total of 752 events will have occurred at the time of the primary analysis. While this sample size gives a power higher than that for the original sample size calculation (90%), it will offer some protection against non-proportional hazards, treatment crossover, loss to follow-up and competing risks (non-CV deaths).

The table below gives the power (and expected number of observed events) under various recruitment and minimum follow-up scenarios.

**Table: Power (and expected number of events [E]) under various recruitment and follow-up scenarios (assuming a 20% control group event rate at 1 year and HR=0.78)**

|                                                                  | 12-month recruitment extension (total recruitment period of 4 years) |                   |                   | 24-month recruitment extension (total recruitment period of 5 years) |                   |                   |
|------------------------------------------------------------------|----------------------------------------------------------------------|-------------------|-------------------|----------------------------------------------------------------------|-------------------|-------------------|
| Monthly accrual for remaining trial duration (from Jan 19)       | 28p/m                                                                | 30p/m             | 32p/m             | 28p/m                                                                | 30p/m             | 32p/m             |
| Expected sample size achieved                                    | 1204 a                                                    | 1244 b | 1284 c | 1540 d                                                    | 1604 e | 1668 f |

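### The primary analysis adjusts only for binary Rockwood frailty and leaves age and recruiting site, a randomisation factor, to a sensitivity model, giving up a modest amount of power

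*Supplement*

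**What the plan says.** Protocol v3.0 section 6.3: "Stratification will be by site and Frailty score", with Rockwood score cut at 5. SAP v2.0 section 2.3 adds that cognitive impairment was a third factor until 14 September 2018: "In total, 532 participants were recruited under the original allocation strategy".

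SAP v2.0 section 5.1.1 uses one of these factors in the primary analysis. The groups are "compared using a non-parametric stratified log-rank test (stratified by Rockwood frailty status at randomisation", and the Cox model for the hazard ratio adjusts for the same binary variable. Protocol section 9.2.1 makes the same choice. A further multivariable model is planned, "as a sensitivity analysis, to also adjust for sex, age at trial entry, MoCA status at baseline and recruiting centre", with centre as a shared frailty term. Appendix 1.2 of the SAP says that the multivariable model targets the same estimand as the main analysis.

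The SAP document history (entry for version 0.4) justifies adjusting for frailty status by an expected improvement in power. Neither document says why site or age is left out of the primary model.

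**The concern.** Two kinds of information are held back from the primary analysis. Site was used to balance allocation, and a test that omits a balancing factor is at most slightly conservative. Age is described in protocol section 1 as a powerful predictor, with adjusted odds of in-hospital death rising 70% per 10 years. The SAP's reason for adjusting for frailty, power, extends in principle to any baseline variable that predicts the endpoint.

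Power is at stake, in a trial with limited room for loss. SAP section 2.5 doubts that the effect persists and puts power at 80% if the hazard ratio rises to 0.90 after two years. Section 3.1 ties the analysis to one year of follow-up for all participants and calculates achieved power for information only, so a shortfall of events would not delay it.

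**Working it through.** **Design inputs (SAP v2.0 section 2.5).** "Assuming an event rate of 20% in the conservative therapy arm at 12 months", 16% in the invasive arm; "then the study will recruit 1668 patients and have 92.5% power (5% two-sided type I error) to observe a HR of 0.78"; "This assumes a total of 752 events will have occurred at the time of the primary analysis"; "To detect a HR of 0.78 with 90% power and 5% two-sided type I error requires around 700 events to be observed". Accrual is 7/24/23/23/23% per year, with analysis one year after the last patient. Section 2.2 gives about 52 centres.

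**Reproducing the plan's figures.**
- Hazard ratio: ln(0.80)/ln(0.84) reversed for invasive against conservative, ln(0.84)/ln(0.80) = 0.7814.
- Power (Schoenfeld): Φ(½·√752·|ln 0.78| − 1.96) = Φ(3.407 − 1.96) = Φ(1.447) = 92.6%. With 0.7814 it is 92.3%. Stated: 92.5%.
- Events for 90% power at 0.7814: Schoenfeld 4·(1.96 + 1.2816)²/(ln 0.7814)² = 691; Freedman 10.51·(1.7814/0.2186)² = 698. Stated: around 700.
- Expected events under exponential survival and the stated accrual: 751, or 747 with the five-year cap. Stated: 752.

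The plan's arithmetic stands. It contains no covariates, so it does not show what adjustment is worth.

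**Value of adjustment, by simulation.** There were 2,500 trials per row, N = 1668, 52 centres of unequal size, blocks of 4 or 6 within site × frailty, and a conditional hazard ratio of 0.78. Assumptions not in the documents: 33% frail with hazard ratio 2, 60% MoCA-impaired, normal site effects with known variance, no loss to follow-up, and the effect sizes in the table.

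| Assumed effects | Age HR per SD | MoCA HR | Site variance | Frailty only | + age, MoCA | + random site effect | Stratified by site × frailty |
|---|---|---|---|---|---|---|---|
| Weak | 1.15 | 1.2 | 0.02 | 90.9% | 91.6% | 91.6% | 88.8% |
| Moderate | 1.30 | 1.3 | 0.05 | 90.0% | 91.0% | 91.4% | 88.1% |
| Strong | 1.5 | 1.6 | 0.15 | 85.7% | 89.1% | 90.9% | 85.4% |

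The Monte Carlo standard error is about 0.6 to 0.7 points per figure. The comparisons within a row are paired, so the differences are more precise.

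- Total gain over frailty only: 91.64 − 90.88 = 0.8; 91.40 − 90.04 = 1.4; 90.88 − 85.72 = 5.2 points.
- Site's share: 0.0, 0.4 and 1.8 points.
- Equivalent extra events, from the squared ratio of mean Z: (3.35/3.31)² = 1.02; (3.31/3.19)² = 1.08; (3.27/2.99)² = 1.20, so about 2%, 8% and 20%.
- Age alone, in a separate simulation: 0.1, 0.8 and 1.8 points, or about 1%, 4% and 9% more events.

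**Type I error (true hazard ratio 1, nominal 5%).** Frailty only rejected 4.2% (moderate) and 4.7% (strong). The model with age, MoCA and a random site effect rejected 4.9% and 5.9%. The standard error is √(0.05·0.95/2500) = 0.44 points, so 5.9% lies two standard errors above nominal, and part of the gain in the strong row may reflect this.

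**The case against.** The strongest reply is that both models are already pre-specified and both will be reported, so the dispute is only about which is labelled primary. That stands as a description. A reader might infer that the plan ignores site; it does not, because centre is in the sensitivity model.

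A reader might also infer that the frailty-only hazard ratio is wrong because adjustment moves it further from 1. That is non-collapsibility: the less adjusted ratio is a valid, less conditional quantity. The simulations also plant 0.78 as the fully conditional ratio, whereas the design derives it from population risks of 20% and 16%. When the effect was rescaled so that the frailty-only ratio was about 0.78, frailty-only power was 0.91 (moderate) and 0.89 (strong). A gain from adjustment remained, but the low baseline in the strong row is partly a matter of calibration.

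Prognostic strength is also largely assumed. The protocol's age figure concerns in-hospital death, and no passage gives a MoCA effect on any outcome. By contrast, protocol section 1 documents the frailty effect on one-year mortality (hazard ratio 4.3), so the power argument does not carry over with equal force.

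The objection to MoCA as a primary covariate stands in full. SAP section 2.3 reports about 7% and later about 13% of patients in the wrong cognitive stratum, with some assessments completed after randomisation in an open-label trial. The protocol's schedule of events marks only Rockwood as required before randomisation. A category for missing values would not cure that.

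It is also fair that the change replaces a non-parametric test with a model-based p-value although the SAP itself doubts a constant effect. That cost is accepted below, with the log-rank test kept as support.

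**Conclusion.** The point holds as a modest loss of efficiency. Site, a randomisation factor, and age, a recognised predictor, are absent from the primary test and model without a stated reason. Type I error is not inflated by the omission, and it would be wrong to conclude that the stated power is mistaken.

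The gain is small under weak to moderate effects and becomes material only if all effects are strong. Most of it comes from the patient-level covariates rather than site. The recommended model, without MoCA, was not simulated in exactly that form; its gain should lie roughly between the age-only and the full figures. Sex was not simulated and no gain is claimed for it. All sizes rest on assumed prognostic strengths and site variances.

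There is a secondary benefit that cannot be sized from the documents. SAP section 5.4 and Appendix 1.1 rest on censoring that is independent given the model's covariates, which is easier to defend with age included.

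**What to change.** Before database lock, amend SAP section 5.1.1 so that the primary Cox model contains Rockwood stratum, continuous age, sex and centre as a shared frailty term, and state that the primary p-value comes from it. If the shared-frailty fit fails, drop centre only. Do not add site as log-rank strata: with about 104 site × frailty cells this gained no power in the simulations and lost about two points in two of the three rows.

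Keep the frailty-stratified log-rank test and the frailty-only Cox model as supportive analyses, and keep MoCA in the sensitivity model. Because the trial statistician has prepared unblinded reports for the data monitoring committee, the blinded senior statistician should approve the change.

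Align SAP sections 5.1.2 (non-proportional hazards), 5.1.3 (competing risks) and 5.4 (the imputation model uses the primary model's variables), the estimand appendix and protocol section 9.2.1.

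Cost: no new data, but more than a single edit. The hazard ratio becomes conditional on more covariates, the p-value becomes model-based, and the primary test gains a convergence fallback.

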#### 5.1.2 Non-proportional hazards

The proportional hazards assumption of the Cox model will be investigated using Schoenfeld residuals (graphically and using the Grambsch-Therneau test – implemented using the estat phtest command in Stata) and by testing the interaction of treatment with log(survival time), i.e. including treatment as a time dependent covariate. In the event that the statistical assumptions of the Cox model are not found to hold then a flexible parametric survival model, adjusted for Rockwood frailty status, will be used to estimate the time-dependent treatment effect (HR) and calculate the restricted mean survival time (RMST). Where there is strong evidence of non-proportional hazards the HR cannot be reliably interpreted and the RMST will take precedence as the primary estimate of the treatment effect. The choice of degrees of freedom, or number of knots, for the restricted cubic spline function and time-dependent effects in the flexible parametric survival model will be guided by model selection criteria, i.e. Akaike's Information Criteria (AIC) and Bayesian Information Criteria (BIC). The fitted survival curves from the model will be overlaid on the Kaplan-Meier curves to graphically assess goodness of fit. The time-dependent HR will be plotted against time with 95% CI's. The RMST is measured as the area under the survival curve up to a specific time,  $t^*$ , and quantifies the average survival (in this case time free from recurrent non-fatal MI or cardiovascular death) from randomisation up to a specific time,  $t^*$ . The value for  $t^*$  will be guided by the last observed event time, as suggested by Royston and Parmar, up to a maximum of 5 years. The RMST in each treatment group, and the absolute difference between treatment groups, will be presented with 95% CI's. The RMST will also be plotted over time for a range of alternative values for  $t^*$ .

The RMST will be calculated and reported regardless of whether the proportional hazards assumption is violated as it can provide a useful summary measure; particularly as a measure of absolute treatment effect (in contrast to the relative treatment effect provided by Hazard Ratios).

The RMST will also be estimated using a flexible parametric survival model, as described above, but without including a time-dependent treatment effect. This estimate will be compared with that

obtained when time-dependent treatment effects are incorporated as another means of assessing the proportional hazards assumption.

### 5.1.3 Competing risks

Given that deaths from other non-CV causes would prevent the occurrence of the primary outcome events, a competing risk analysis with the competing event being non-CV death will be performed as a supplementary analysis. Cumulative incidence of non-fatal MI or CV-death will be estimated, taking into account competing risks, using the Aalen-Johansen method and summarised by cumulative incidence curves. Estimates of 6-month and 1-year cumulative incidence will be reported in each treatment group (with 95% CI's). Estimates of the treatment effect would be made using Fine and Gray's proportional regression model, adjusted for Rockwood frailty status, and presented as the sub-distribution hazard ratio (sHR), with a 95% CI. A potential limitation of the Fine and Gray approach is the sum of the cause-specific cumulative incidence functions can sum to more than one for some covariate patterns. We will investigate the impact of this potential limitation by calculating total failure probabilities for all subjects at 1, 3 and 5 year follow-up.

As above, if the proportional hazards assumption is not found to hold, flexible parametric models would be used to estimate the time-dependent sHR and the difference in RMST between treatment groups. Cause-specific cumulative incidence curves will also be provided.

An additional supplementary analysis will incorporate non-CV deaths into the composite outcome measure. Time to all-cause death or non-fatal MI will be measured as the time from randomisation to death from any cause or non-fatal MI, whichever is earliest. Patients alive and free from recurrent non-fatal MI at the time of analysis will be censored at the date they were last seen or assessed. A Cox proportional hazards model, adjusted for Rockwood frailty status, will be used to estimate the treatment effect and a stratified log-rank test will be used to compare the difference in survival between treatment groups. As described in section 5.1.2, the proportional hazards assumption will be investigated, and a flexible parametric survival model used to estimate the time-dependent HR and RMST if the proportional hazards assumption is violated.

